### Statistical analyses

The intention-to-treat principle will be followed, where all participants who completed the baseline questionnaire will be included in the analysis regardless whether they complete the whole intervention. Acknowledging there may be attrition at the follow-up, the missing values for the non-respondents will be recorded using their baseline scores. If the missing data are at random, the imputation method will be applied [59]. This will assure no false improvement in efficacy. Data will be analysed using SPSS Version 22.

The demographics of the participants in the intervention and control groups will be compared using the independent samples t-test or Pearson’s Chi-square test to measure differences including age, gender and country of birth. The primary outcome measures (described above) will be calculated following validated MHFA scoring methods reported in the literature [44,54,57,65-68]. Repeated measures analysis of variance will be employed to assess continuous measures between the intervention and control group over three time points (baseline, post intervention and two months post intervention). Logistic regression will be used to assess changes in dichotomous variables. The significance level will be set at 5%.

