#### Stage 4: post-intervention questionnaire one

Immediately after course completion, the intervention group will be asked to complete the post intervention questionnaire in the classroom via i-pad. The control group will be emailed the same questionnaire at the same time. An email reminder will be sent twice a week for two weeks to those who do not respond in the first instance.

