#### Stage 5: post-intervention questionnaire two

Two months after the MHFA course is delivered, the second post-intervention questionnaire will be emailed to all participants. An email reminder will be sent twice a week for two weeks to those who do not respond in the first instance.

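### Filling missing follow-up scores with baseline scores does not guarantee against false improvement, and the plan's two missing-data rules are not reconciled

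*Protocol article*

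**What the plan says.** Under Statistical analyses, the protocol article defines the analysis set so that "all participants who completed the baseline questionnaire will be included in the analysis regardless whether they complete the whole intervention". For those who do not respond at follow-up, "the missing values for the non-respondents will be recorded using their baseline scores". The next sentence reads: "If the missing data are at random, the imputation method will be applied". The method is not named; a reference is cited. The paragraph then concludes: "This will assure no false improvement in efficacy".

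The response routes are set out under Stages 4 and 5. At the first follow-up, "the intervention group will be asked to complete the post intervention questionnaire in the classroom via i-pad", whereas for controls: "The control group will be emailed the same questionnaire at the same time". Non-respondents get email reminders twice a week for two weeks. At two months the routes are the same: "the second post-intervention questionnaire will be emailed to all participants".

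Participants and sample size allows for 20% attrition in each group and gives no separate rate by arm.

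**The concern.** Filling with the baseline score assigns exactly zero change to every non-respondent. That is cautious only in some circumstances. If scores rise in both arms for reasons unrelated to the course, such as seeing the same knowledge questions again, the fill removes part of that rise from each arm in proportion to its missing share. If the shares differ, the remainder is counted as a treatment effect. If they are equal, the fill dilutes any true effect.

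Unequal shares are possible at the first follow-up, because one arm answers in a classroom and the other answers an emailed link. The stated assurance would lead a reader to treat a positive result as safe from this problem, which it is not.

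The second rule adds a further difficulty. Whether data are missing at random cannot be established from the observed scores, so the condition gives the analyst no workable way to choose between the two methods.

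**Working it through.** **Inputs from the protocol article.** 50 per group before attrition, 20% attrition, baseline-post correlation 0.8, 5% significance (Participants and sample size; Statistical analyses).

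**Inputs assumed.** True effect D = 0.5 SD where an effect is present (the article says only that it is medium), common gain c, and missing shares m_I and m_C. Missingness is unrelated to change. Scores have SD 1.

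**The plan's own figure.** 50 / (1 − 0.20) = 62.5, rounded up to 63 per group. This reproduces.

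**Expected estimate under baseline fill.** Mean change is (1 − m_I)(c + D) in the intervention arm and (1 − m_C)c in the control arm. The difference is

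D(1 − m_I) + c(m_C − m_I).

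- Equal missingness at the planned rate, D = 0.5: 0.5 × 0.80 = 0.40 SD, a loss of one fifth, whatever c is.
- D = 0, c = 0.3, 5% missing in intervention and 35% in control: 0.3 × 0.30 = +0.09 SD.
- D = 0, c = 0.3, 10%/30%: 0.3 × 0.20 = +0.06 SD.
- D = 0, c = 0.3, 15%/25%: 0.3 × 0.10 = +0.03 SD.
- D = 0, c = 0.1, 5%/35%: 0.1 × 0.30 = +0.03 SD.
- D = 0, c = 0.3, 35%/5%: 0.3 × (−0.30) = −0.09 SD.

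The 5%/35%, 10%/30% and 15%/25% patterns all average to the planned 20% overall.

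**Type I error, simulated.** 63 per arm, correlation 0.8, test on change from baseline, nominal 5% two-sided, D = 0:

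| Common gain | Missing, intervention/control | Type I error |
|---|---|---|
| 0.3 SD | 20%/20% | 5% |
| 0.1 SD | 5%/35% | about 6% |
| 0.3 SD | 15%/25% | about 6% |
| 0.3 SD | 10%/30% | about 9% |
| 0.3 SD | 5%/35% | about 15% |

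In the last two rows nearly all rejections favoured the intervention. With the pattern reversed (35%/5%, gain 0.3 SD), the rejection rate was also about 15%, almost all against the intervention.

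**Hand check of the 15% row.** The change score has variance 2(1 − 0.8) = 0.4. After filling, the variance in an arm is (1 − m) × 0.4 + m(1 − m)c². Intervention: 0.95 × 0.4 + 0.0475 × 0.09 = 0.384. Control: 0.65 × 0.4 + 0.2275 × 0.09 = 0.280. The standard error is √((0.384 + 0.280)/63) = 0.103, and the shift is 0.09/0.103 = 0.88 standard errors. The normal approximation then gives about 14% rejection, in line with the simulation.

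**The planned three-time-point analysis.** Simulating the group-by-time test of the repeated measures analysis of variance, with unequal missingness at the first follow-up only and 20% in each arm at two months, gave 12% to 13% (gain 0.3, 5%/35%), about 8% (gain 0.3, 10%/30%), 5.6% (gain 0.3, 15%/25%) and 5.8% (gain 0.1, 5%/35%). Equal missingness gave 5.3%. The pattern survives in the planned model.

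**The case against.** The strongest defence has four parts.

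**Equal attrition.** The article plans the same attrition for both groups. Under that plan the fill shrinks the estimate, which fits the authors' aim of caution. This stands as far as it goes. In simulation with D = 0.5, no common gain and 20% missing in both arms, power barely moved (97.0% with the fill, 97.4% on observed scores), so the harm there is an understated effect rather than a lost trial. It does not save an unconditional assurance.

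**More missing controls is not a fact.** A reader might infer from the two response routes that more controls will be missing. The document does not support that. It gives no rate by arm and it plans repeated reminders. Controls receive the online course only after the second questionnaire, which may keep them engaged. Stage 6 also expects some intervention students not to complete the training, and they may not be in the classroom to answer. The routes differ only at the first follow-up.

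**The common gain is assumed.** Baseline is one week before the intervention and the courses run over two weeks, so ordinary teaching has little time to raise scores by the first follow-up. Retest learning is credible mainly for the 16 knowledge questions, less so for stigma and social distance. The larger error rates should not be read across to every outcome.

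**The missing-at-random sentence may govern.** On one reading, baseline fill is only the fallback when data are not missing at random, and the simulated cases would then be imputed. The text allows that reading, so baseline fill cannot be called the primary rule with certainty. But the fill is stated first and without condition, the other method is unnamed, and its trigger cannot be verified. A reader might go further and infer that the method will be picked after results are seen. The article does not show that, and a separate analysis plan could settle the choice.

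**Conclusion.** The concern holds in limited form and should be fixed. The assurance against false improvement is wrong as a general statement, and the two missing-data rules are left unreconciled.

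The shrinkage from 0.50 to 0.40 SD needs only the planned 20% attrition in both arms, missingness unrelated to change, and an assumed effect of 0.5 SD. A false benefit needs two further conditions together: change common to both arms, and more missing controls than intervention students. Over the range examined, type I error is near nominal (about 6%) under mild assumptions, about 9% in the middle and about 15% at the strong end. The bias is −0.09 SD when the imbalance runs the other way with a 0.3 SD gain. If non-respondents actually got worse, the fill would hide that in whichever arm they belong to.

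The document does not support saying that the trial will report a false effect, or that the 15% figure is the expected error rate. It mentions no confidence intervals, so no claim about stated coverage is made here. What is established is that the direction and size of the bias depend on a response pattern that the plan does not control.

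**What to change.** - Make the primary analysis of the continuous outcomes a likelihood-based mixed model for repeated measures on all observed scores, with arm, time and their interaction and with account taken of the baseline score. Multiple imputation within arm, using baseline score and demographics, is an acceptable alternative.
- Keep baseline-carried-forward only as a sensitivity analysis, labelled as such.
- Delete the sentence that promises no false improvement, and delete the switch that depends on data being missing at random.

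This changes analysis wording only; recruitment, questionnaires and timing stay as they are. The downside is that the primary analysis then relies on missing at random. Observed-score analysis held 4.8% to 5.2% error in the simulations, but missingness there was generated completely at random, so that result does not show it would hold if non-respondents differ from respondents. The sensitivity analysis is there to probe that.

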The Australian Government Department of Health has provided funding to Mental Health First Aid Australia [62] to specifically train frontline staff including financial counsellors and healthcare professionals (including pre-service nursing students) to better identify and respond to the needs of people at risk of mental health problems and disorders. The aim of the course developed for nursing students is to teach them how to assist a peer who is developing a mental health problem or in a mental health crisis. The course is available both as a face to face version and as an e-course online [63].

This paper presents a protocol for a pragmatic, low-cost trial to examine the efficacy of the MHFA training for students studying nursing at a large university in Perth, Western Australia. The primary outcome is changes in mental health literacy, which will be measured in terms of confidence in dealing with mental health problems, recognition of and knowledge about mental health problems, first aid intentions, stigmatising attitudes and social distance.

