**Trial schema.**

### Participants and sample size

The source population will be undergraduate nursing students at a large university located in Perth, Western Australia. Criteria for inclusion: 1) first year undergraduate nursing student; 2) enrolled in the internal study mode; 3) studying at the Curtin University Bentley campus; and 4) aged 18 years or older. The size of the sample has been determined by the practicalities of working in a large university which requires delivering the intervention during semester at a time convenient to university scheduling requirements and clinical rotations for the students. Assuming a high correlation of 0.8 for the baseline-post measurements [65,66], it will be necessary to have 50 students in each group to detect 5% level of significance with 90% power in order to detect medium effect sizes in the outcome variables [57]. A total of 63 students will be recruited for each group to account for 20% attrition from baseline to post intervention.

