### Instruments

A self-report questionnaire will measure confidence to respond to mental health problems, recognition of and knowledge about mental health problems, first aid intentions towards someone experiencing a mental health problem, stigmatising attitudes [67] and social distance [68-70]. The questionnaire is based on those used in national surveys of adults [43] and young people [71] and further developed for use with the MHFA course [54,65,69], and described in detail in previous studies [44,57,72]. Questions related to confidence, recognition, intentions, stigmatising attitudes and social distance will be introduced with a vignette describing a young person with symptoms of a mental health problem. The use of the vignette to introduce mental health issues has been used successfully by other studies, including those of MHFA [44,57,68,72]. Participants will be asked about their level of confidence to help and what they would do to assist the person in the vignette [65]. Knowledge will be measured using 16 questions developed by MHFA and modified for use with young people [66]. Stigmatising attitudes will be measured using personal and perceived stigma scales [67], and social distance will be measured using a five item social distance scale [68]. The scales have been used widely and previously tested for reliability and validity; the stigma scales have demonstrated test-retest reliability and acceptable internal consistency while the social distance scale has been shown to be a reliable measure of stigma towards people with mental health problems and to be valid as a proxy measure for rejection of and discrimination toward people with mental health problems and disorders [67,69,70,73]. The questionnaire will be administered to the intervention and control group participants at three time intervals: baseline, immediately post, and two months after the intervention. Basic socio-demographic characteristics of participants will be collected at baseline only.

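### The repeated-measures ANOVA takes baseline as an outcome level and names no contrast, so its omnibus group-by-time test alone cannot show that an effect persists at two months

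*Protocol article*

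**What the plan says.** The Statistical analyses section of the protocol article fixes the method for continuous outcomes: "Repeated measures analysis of variance will be employed to assess continuous measures between the intervention and control group over three time points". The three times are listed as "baseline, post intervention and two months post intervention", so the pre-training score is an outcome level and not a covariate. The section does not say whether efficacy is judged by the group main effect, by the group-by-time interaction or by a contrast at a given time.

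The primary outcome gives little further direction. The Mental health first aid section says "The primary outcome is changes in mental health literacy", covering several domains, without naming a time. The sample size section begins "Assuming a high correlation of 0.8 for the baseline-post measurements", which suits a change-score or baseline-adjusted comparison but is not tied to the three-level ANOVA.

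For binary outcomes the plan is one sentence: "Logistic regression will be used to assess changes in dichotomous variables". According to the Instruments section, both groups answer the questionnaire "at three time intervals: baseline, immediately post, and two months after the intervention", so any dichotomous item is repeated within a student.

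**The concern.** Before training the arms can differ only by chance. Putting that time into the outcome vector has two consequences. The group main effect averages a true zero with the follow-up effects. The group-by-time test asks only whether the arm difference varies over the three times, and it does so whether the training effect persists, fades or appears late.

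Persistence matters in this trial. The Mental health first aid section notes that few studies show longer-term impact. Controls are offered the online course after the two-month questionnaire (Ethical approval; Stage 6), and the 12-month follow-up covers the intervention group only (Stage 8). Two months is therefore the last randomised comparison. A headline p-value that is equally likely to be significant when the effect has gone does not answer that question.

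**Working it through.** **Inputs.** From the article: 50 per arm analysed, 5% significance, 90% power, baseline-post correlation 0.8, 20% attrition. Assumed: two-sided testing; d = 0.5 SD for a medium effect, since no number is given (0.3 also shown); correlation ρ = 0.8 between all pairs of times, although the article gives it only for baseline-post; equal variances.

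**The plan's own figure.** 50/(1 − 0.20) = 62.5, so 63 per group reproduces. The 50 cannot be checked uniquely without a number for the effect. With n = 2(1.96 + 1.2816)²σ²/d² at d = 0.5:
- unadjusted, σ² = 1: 85 per group;
- change score, σ² = 2(1 − 0.8) = 0.40: 34 per group;
- baseline-adjusted, σ² = 1 − 0.8² = 0.36: 31 per group.

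Fifty per group corresponds to d of about 0.41 (change score) or 0.39 (baseline-adjusted). That mismatch is separate and does not alter what follows.

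**Group-by-time test.** λ = (n/2) Σ(δₜ − mean δ)² / (1 − ρ), on 2 and 196 df.
- Kept, δ = (0, 0.5, 0.5): mean 0.333, sum of squares 0.1667, λ = 25 × 0.1667/0.2 = 20.8.
- Lost, δ = (0, 0.5, 0): mean 0.167, sum of squares 0.1667, λ = 20.8.

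Power is 98.7% for both. Simulation with 4,000 runs gave 98.5% (kept) and 98.8% (lost). At d = 0.3, λ = 7.5 and power is 68.1% for both.

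**Group main effect.** λ = (n/2)(mean δ)² / [(1 + 2ρ)/3], where (1 + 1.6)/3 = 0.867.
- Kept: 25 × 0.1111/0.867 = 3.2, power 42.6%.
- Lost: 25 × 0.0278/0.867 = 0.80, power 14.4%.

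**Contrast at two months (effect kept).**
- Baseline-adjusted: 0.5/√(2 × 0.36/50) = 0.5/0.12 = 4.17 on 97 df, power 98.5%. At d = 0.3 it is 2.5, power 69.7%.
- Change score: 0.5/√(2 × 0.40/50) = 3.95 on 98 df, power 97.5%.

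Both reject at the nominal 5% if the effect has gone by two months.

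| Test (n = 50, d = 0.5, ρ = 0.8) | Effect kept | Effect lost |
|---|---|---|
| Group-by-time, 2 df | 98.7% | 98.7% |
| Group main effect | 42.6% | 14.4% |
| Two-month change contrast | 97.5% | 5% |
| Two-month baseline-adjusted contrast | 98.5% | 5% |

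If the true correlation were 0.5, the variances would be 1 − 0.25 = 0.75 (adjusted) and 2(1 − 0.5) = 1.00 (change), so adjustment would gain more.

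**Binary outcomes.** This was simulated under no effect with 50 per arm, a latent normal variable with correlation 0.8, 50% prevalence and 3,000 runs. A logistic model at two months rejected 6.0% without baseline and 4.6% with baseline status as covariate. Stacking rows and ignoring the correlation rejected 13.6% (two follow-up rows) or 20.5% (three rows) for the arm term. A stacked arm-by-time term erred the other way: 0.3% rejection, and 19% power against 64% for the per-time adjusted model.

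**The case against.** The strongest reply is that repeated-measures ANOVA can carry time-specific contrasts. The article neither states nor excludes them, and naming them is normal content for a fuller analysis plan. A two-month change contrast within the planned framework has 97.5% power, close to the adjusted 98.5%. This stands against any inference that the method itself cannot tell a lasting effect from a lost one: the limitation belongs to the omnibus test read alone. A significant interaction also validly shows that the arms' trajectories differ, and the means would show the pattern. What remains is that the article fixes baseline as an outcome level and leaves the deciding test open.

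Three further readings are tempting and not supported.
- **The trial is underpowered.** The 43% and 14% figures apply only if the group main effect is the test. An outcome defined as change points to the interaction.
- **The logistic regression ignores the repeated data.** The sentence specifies neither stacked rows nor an unadjusted model. A model fitted at one time is valid, so this is an ambiguity and not a demonstrated error.
- **SPSS dropping incomplete cases drove the choice of baseline carry-forward.** The article gives a different reason, namely to avoid false improvement, and filled values would not be dropped.

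**Conclusion.** The point holds for the continuous outcomes. As written, the plan's default omnibus test gives the same power, 98.7%, whether the effect is kept or lost at two months, so significance alone is not evidence of persistence. The exact equality rests on equal variances and equal correlations across the three times. Under those conditions it holds for any effect size, and the power is 68% in both cases at d = 0.3. The general point, that an omnibus test does not identify which time differs, does not depend on those conditions.

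The gain from a baseline-adjusted contrast lies mainly in answering a defined question. Its precision gain over change scores is modest at correlation 0.8 (variance 0.36 against 0.40) and larger if the correlation is lower. For binary outcomes there is only a wording gap to close. This should be changed, but it does not invalidate the design.

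**What to change.** **Continuous outcomes.** Replace the three-level ANOVA with a mixed model (SPSS MIXED), or ANCOVA at each time, with the two follow-up scores as outcomes and the baseline score as covariate. The mixed model has terms for arm, time and arm-by-time. Report the adjusted arm difference with its confidence interval immediately after training and at two months, and name in advance which is primary. Two months is the last randomised comparison, but the article does not rank the times and the choice is the sponsor's.

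**Dichotomous outcomes, as a secondary clarification.** State that the logistic model is fitted at each follow-up with arm and baseline status as covariates, or that a logistic GEE with robust standard errors is used.

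**Cost.** Analysis wording only: no new data, the same software and no change to the planned 50 per arm, which gives 90% power for the adjusted contrast at d of about 0.39 or more under ρ = 0.8.

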## Discussion

Trialing strategies to reduce the burden of mental health problems and disorders in the setting where students socialise, live and study is important and will likely influence their attitudes post university towards mental health and wellbeing and those living with mental health problems and disorders. Due to the voluntary nature of participation in this intervention, selection bias may occur, however the randomisation of the treatment allocation used in this study attempts to reduce this effect. Findings including the efficacy and implications from this study will therefore provide information supporting the early implementation of MHFA training for nursing students to increase their mental health literacy and thus potentially improve future mental health care delivery. MHFA training has limited research regarding its implementation in young adults. If this intervention demonstrates the scalability of MHFA in the university environment for pre-service nurses, it could provide support for teaching mental health first aid across a wider variety of university courses. It is anticipated that implementation of MHFA courses, with comprehensive evaluation, could yield positive improvements in the mental health literacy amongst this target group.
